## Abstract

**Background:**

Osteoarthritis (OA) is a major cause of pain and disability worldwide. Despite the relatively high burden of the disease, the currently available non-surgical treatment options are directed towards symptomatic relief. Therefore, we propose the use of alendronate as a disease modifying agent to help slow and prevent OA. In addition, this study will utilize Whole-Organ Magnetic Resonance Imaging Score (WORMS) to evaluate the structural integrity of cartilage in the study population. High-quality evidence, limited to a few well-conducted randomized trials, highlights contradictory results on the effect of bisphosphonates on knee function and progression of OA. Therefore, a placebo-controlled, randomized trial is needed to evaluate the combined effect of alendronate and vit D on the structure of cartilage utilizing the WORMS score and its ability to treat knee pain in OA patients.

**Methods:**

This multicenter, randomized, double-blinded, placebo-controlled study will evaluate the efficacy and safety of alendronate in early OA. Patients will undergo a 1:1 double-blinded randomization to receive a one-year course of either alendronate sodium vitamin D_3_ or placebo. The primary outcome is to compare WORMS score of knee joint at 6 and 12 months between both groups. Secondary endpoints will include WORMS score at 24 months, knee pain, radiographic progression of OA, severity of OA, quality of life, and serum inflammatory biomarkers at different assessment timepoints. To detect a 2.2% difference in cartilage loss between both groups with power of 80%, a sample size of 60 (30 per group) is proposed.

**Discussion:**

This trial will give helpful and high-quality evidence regarding the potential therapeutic role of alendronate sodium vitamin D3, as compared to placebo, in the management of patients with knee OA regarding its role on cartilage loss, radiographic progression of OA, severity of OA, knee pain, quality of life, and inflammatory biomarkers. If proven effective, this intervention would be a great option for providing beneficial outcomes with a reduced cost in this patient population.

**Trial registration:**

This trial was registered on clinicaltrials.gov (registration number: NCT04739592).

**Supplementary Information:**

The online version contains supplementary material available at 10.1186/s12891-022-05521-4.

## Background

Osteoarthritis (OA) is a major cause of pain, functional limitations, and disability worldwide [1]. The hip and knee joints are the most common sites of OA-associated disability worldwide [2]. The causes of pain and mechanical dysfunction in osteoarthritis (OA) remain unclear, and previous research have suggested multifactorial causes [3–6]. Injury to one component of the joint leads to a cascade of injuries that lead to further joint dysfunction and clinical manifestations of OA. Currently, only a few features, such as joint space narrowing and osteophytes can be detected on standard radiographs, and determining the severity of disease is limited. Therefore, a broader imaging assessment scale is needed to correctly evaluate joint structural integrity and its role in the symptomatic manifestations of OA.

The Whole-Organ Magnetic Resonance Imaging Score (WORMS) is a good semi-quantitative tool for the study of knee osteoarthritis (KOA). The WORMS score includes cartilage signal and morphology, subchondral bone marrow abnormalities, subchondral cysts, subchondral bone wear, marginal osteophytes, and other features which can comprehensively analyze the morphology and structure of knee OA. The WORMS scoring system requires magnetic resonance imaging (MRI), which not only has no ionizing radiation, but also avoids the morphological aberration, amplification, and superposition seen with computer tomography. More importantly, MRI is well suited for evaluating joint tissues such as cartilage, meniscus, and ligaments, giving it great potential as an imaging tool for the entire joint. The knee MRI scans will be taken using a 1.5-T whole-body MRI unit with a transmit-receive coil. The same scanning unit will be used for all participants in the study center. The sequence and parameters of the used MRI unit is provided in (Supplementary Table 1).

For osteoarthritis (OA), current treatments focus on symptomatic relief, but many patients do not achieve adequate pain control [7]. In addition, despite the high prevalence of OA, there are currently no approved disease-modifying drugs (DMOADs) for OA that would help prevent the joint damage seen along the course of the disease. Therefore, the development of a novel and effective treatment is necessary.

Bisphosphonates are a class of drugs commonly used to treat osteoporosis due to their ability to inhibit osteoclast-mediated bone loss. Several studies have reported favorable results of bisphosphonates as a potential treatment option in osteoarthritis. In animal studies, bisphosphonates (alendronate, tiludronate) have demonstrated the ability to slow the progression of OA-related structural damage [8–10]. Similarly, a clinical study found that the use of bisphosphonates (including ibandronate, pamidronate, risedronate, and zoledronate) to be associated with a 26% reduction in the risk of knee replacement in older women [11].

In 2017, a meta-analysis was conducted to compare the efficacy of bisphosphonates to placebo in patients with knee OA in terms of knee pain, radiographic progression, and adverse events [12]. Based on the analysis of seven randomized controlled trials, no statistically significant differences were noted between both groups regarding knee pain and function, radiographic progression, or adverse events. However, no subgroups analyses were reported regarding the type of bisphosphonate, dose or route, assessment timepoint, or measurement scale.

During the first 3 years of observation, alendronate which was most commonly used (> 60%) in the Osteoarthritis Initiative (OAI) [13] showed a reduction in knee pain for the women taking the medication. Additionally, joint space narrowing (JSN) decreased over time in bisphosphonate users. Alendronate has also been found to delay progression of spinal osteophytes and disc space narrowing suggesting it may be able to slow the progression of spinal osteoarthritis [14].

High-quality evidence, limited to a few well-conducted randomized trials, highlights contradictory results on the effect of bisphosphonates (of different doses and administration routes) on knee function and disease progression in patients with knee OA [15–17]. Furthermore, another ongoing multicenter, randomized, double-blinded, placebo-controlled trial will compare the efficacy of annual infusions of zoledronate to placebo in terms of knee joint structural changes and knee pain in patients with knee OA [18]; however, the results are expected in 2022–2023. Therefore, and based on the above-mentioned observations, we are willing to conduct this randomized, placebo-controlled trial to determine the effect of combined alendronate sodium with vit D on the knee joint structure, knee pain, radiographic grade of OA, quality of life (QOL), and severity of OA in patients with knee OA and MRI evidence of bone marrow edema-like lesions since they show greater response to bisphosphonates [19].

### Trial objectives

This designed randomized controlled trial will explore the efficacy of alendronate sodium vitamin D_3_ compared to placebo on the improvement of joint structure and pain in patients with knee osteoarthritis. Our primary hypothesis is that there will be a significant improvement in the joint structure, as measured by the WORMS scale, in favor of alendronate at each assessment timepoint. Our secondary hypothesis is that there will be a significant improvement in knee pain, severity of OA, and quality of life, as well as a significant reduction in the level of inflammatory biomarkers, among patients assigned to the alendronate sodium vitamin D3 as compared to those given placebo.

## Methods/design

### Study design and setting

This is a multicenter, randomized, double-blinded, placebo-controlled study. Upon obtaining Institutional Review Board (IRB)- Ethics Committee’s approval (from each corresponding included center), recruitment of patients will begin. The study is scheduled to start on May 1, 2021, with a completion date on December 31, 2022. Patients will undergo a 1:1 double-blinded randomization to receive a one-year course of alendronate sodium vitamin D_3_ tablets (Gubangjia, The CSPC Ouyi Pharmaceutical Co., Ltd. Shijiazhuang, China) or placebo. The use of Tylenol for pain control will be permitted during the trial; however, it will be monitored and reported for future analysis. In addition, Vitamin D and calcium supplementation will be allowed for usage by study participants. The use of unmarketed drugs or other investigational drugs will be prohibited during the study period; otherwise, such patients will be excluded. Other bisphosphonates (such as zoledronic acid, risedronic acid, etc.) will be prohibited during the study period. Non-steroidal anti-inflammatory drugs and other topical drugs with analgesic effects will be prohibited during the study period. This study will be carried out in three domestic hospitals (Peking Union Medical College Hospital, Zhongshan Hospital of Fudan University, and The Third Affiliated Hospital of Southern Medical University) with a follow-up period of 2 years.

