#### Exclusion criteria

Patients will be excluded if they have one of the following criteria: (1) having any forms of active arthritis (such as rheumatoid arthritis or other inflammatory arthritis), (2) users of non-steroidal anti-inflammatory drugs (NSAIDs) and central analgesics (such as opioids) within two weeks or other study drug or device within 30 days before randomization or within the drug half-life (whichever is longer), (3) evidence of abnormal liver function tests (ALT or AST; at least a 1.5-fold increase above the upper limit of normal), (4) having renal dysfunction, osteomalacia, or creatinine clearance < 35 mL/min, (5) having serious heart disease, endocrine, digestive, mental, nervous system diseases, cancer, or serious illnesses with a life expectancy of less than two years, (6) pregnancy or breast-feeding, (7) having active ulcers, history of upper gastrointestinal bleeding, or esophageal motility disorders, (8) having fracture within 6 months of study initiation, (9) tobacco addiction or alcohol abuse, (10) having allergy or contraindication to study medications, (11) contraindications to MRI or X-rays exposure, (12) planned joint replacement within the study period, or (13) having poor dental health or scheduled dental surgery before or during the study period.

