### Outcome measures

#### Primary outcome

Our primary outcome is to determine the improvement in knee structure following each intervention using an MRI-based scale named the Whole-Organ Magnetic Resonance Imaging Score (WORMS) scale at 6 and 12 months after treatment allocation [20]. The WORMS scale is designed to determine the status of the knee joint in patients with OA in respect to fourteen independent articular features. Five out of the 14 features are related to the articular surfaces, and they include: (1) cartilage signal and morphology, (2) subarticular bone marrow abnormality, (3) subarticular cysts, (4) subarticular bone attrition, and (5) marginal osteophytes. In addition, all of these features are further evaluated in 15 different regions divided by anatomical landmarks in a fully-extended knee (Supplementary Fig. 1). For the purposes of our research, we will focus on cartilage signal and morphology. This feature is scored based on only 14 articular surface regions (excluding region S), with a score ranging from 0 to 6 on an 8-point scale (Supplementary Fig. 2). The WORMS scoring system for cartilage includes 0 = normal cartilage thickness and signal, 1 = normal cartilage thickness but with increased signal, 2 = a partial-thickness defect of < 1 cm in the greatest width, 2.5 = a full-thickness focal defect of < 1 cm in the greatest width, 3 = multiple regions having partial-thickness defects alternating with regions of normal thickness or defects > 1 cm, 4 = diffuse partial-thickness defects, 5 = multiple regions of full-thickness defects or defects > 1 cm, and 6 = diffuse full-thickness defects, with an overall score ranging from 0 to 84.

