#### Secondary outcomes

We have seven pre-identified secondary outcomes: WORMS score (at 24 months), pain intensity (at 2, 4, 8, and 12 weeks after enrollment), quality of life (QOL), bone density, risk of knee replacement, severity of knee OA, and estimation of inflammatory biomarkers.The structure of knee joint will be measured using the WORMS scale at 24 months after treatment.Knee pain will be measured in both groups at 2, 4, 8, and 12 weeks after enrollment using the 100-mm visual analogue scale (VAS), which has already been shown to be valid and reliable in measuring pain [21]. Overall ratings range from 0 to 100 mm, where 0–4 mm indicate no pain, 5–44 mm indicate mild pain, 45–74 mm indicate moderate pain, and 75–100 mm indicate severe pain.Quality of life in both groups will be assessed at 3, 6, and 12 months after enrollment using the previously validated Chinese version of the SF-36 questionnaire [22], which is used to measure health status based on eight categories: (1) physical activity, (2) social activity, (3) physical role, (4) energy and emotional status, (5) mental health, (6) vitality, (7) body pain, and (8) general health. The overall score ranges from 0–100, with higher scores reflecting better health-related QoL [23]. This version of the SF-36 questionnaire shows comparable validity and reliability to the original version.Bone density of the lumbar spine and the hip and knee joints will be carried out using dual-energy x-ray absorptiometry (DXA) at 12 and 24 months after enrollment. Bone density data will be obtained using a Prodigy DXA scanner (GE Healthcare, Madison, USA) and the obtained data will be analyzed according to the manufacturer’s software. The lumbar spine (L1-L4) and the hip (particularly the femur neck and total hip) will be scanned in the supine position using posteroanterior projections.The risk of knee replacement will be evaluated based on a set of baseline and clinical variables and then incorporated into a multivariable logistic regression model to identify significant predictors of knee replacement in patients with OA.Severity of OA will be measured at 12 and 24 months after enrollment using the Kellgren-Lawrence grading scale [24]. The scores of this grading scale range 0 to 4, where 0 indicates no features of OA, 1 indicates questionable osteophytes, 2 indicates definite osteophytes without narrowing in the joint space, 3 indicates definite osteophytes with moderate narrowing, and 4 indicates definite osteophytes with severe narrowing.The serum level of the following inflammatory biomarkers will be measured at 3, 6, and 12 months after enrollment: interleukin (IL)-6, tumor necrotic factor (TNF)-alpha, erythrocyte sedimentation rate (ESR), and C-reactive protein (CRP).

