### Sample size calculation

Based on a previous observation, the mean annual loss of the medial tibial cartilage volumes in knee OA patients is 4.5% [25]. The monthly intake of vitamin D (50,000 IU) would result in a serum vitamin D3 level > 60 nmol/L [26], and this, in turn, has been reported to correlate with a 2.2% annual absolute reduction in cartilage loss [27]. This can be translated into a risk reduction of 22% for knee replacement over a period of 2 years [28]. Our sample size calculation was conducted based on Cohen’s formula [29]. With a power level of 80% and alpha level of 0.05, 60 participants (30 in each group) were required to detect a 2.2% between-group difference in terms of medial tibial cartilage loss (WORMS scale) during the second assessment time-point (12 months). Losses to follow-up were not considered in our initial sample size calculation (*NCT04739592*); however, given the fact that both interventions will be administered for a year and patients will be followed up for 2 years after enrollment, we anticipate that around 10% will be lost to follow-up each year, so we increased our final sample size to 220 participants (110 in each group).

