### Statistical analysis

Retrieved data from each patient in both groups will be recorded at baseline and at each follow-up assessment period using Excel, which will then be entered into a software for analysis after the final assessment point has been met. All statistical analysis will be conducted by a third-party (not involved with our research in any way) using the Statistical Analysis System (SAS) Software for Windows (version 9.4, *SAS institute, USA*).

Baseline demographic and clinical variables will be presented in the form of number and percentages for categorical variables, while continuous variables will be presented as means and standard deviations (SD) or median and range if the data were normal or skewed, respectively.

Our primary outcome will be analyzed with the intention-to-treat (ITT) analysis and reported as the mean difference (MD) and corresponding 95% confidence interval (CI) in cartilage-WORMS score between the intervention and control groups using Student’s t-test. Secondary outcomes will then be analyzed at the final assessment. Pain will be analyzed as a categorical outcome using the chi-square test, while the differences in continuous determinants of pain (baseline variables) will analyzed using MANOVA test. The QoL will be analyzed and reported as the mean difference and its corresponding 95% CI between both interventions using t-test. Bone density and osteoporosis severity (measured by the Kellgren-Lawrence scale) will be analyzed as categorical outcomes (normal, low density, osteoporosis) using the Chi-square test. Meanwhile, differences in serum levels of inflammatory biomarkers between both groups will be measured using t-test. In order to account for missing data, survival analyses will be conducted while implementing the “last-observation carried forward” approach. Such data will be presented in Kaplan–Meier curves, showing the numbers of patients analyzed at each assessment timepoint. A *p*-value of less than 0.05 will indicate statistical significance.

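### Bisphosphonates are barred only during the study, with no look-back at entry, so recent users can be randomised; if effects persist, the contrast is attenuated by an amount the protocol cannot size

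*Protocol article*

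**What the plan says.** The Study design and setting section of the protocol article restricts the class on study: "Other bisphosphonates (such as zoledronic acid, risedronic acid, etc.) will be prohibited during the study period". That sentence is the only restriction on bisphosphonates in the article.

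The Exclusion criteria do set look-backs for other drugs, both in criterion 2. One covers "users of non-steroidal anti-inflammatory drugs (NSAIDs) and central analgesics (such as opioids) within two weeks". The other covers "other study drug or device within 30 days before randomization or within the drug half-life (whichever is longer". No criterion names bisphosphonates, and the Inclusion criteria do not ask for patients naive to the class.

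The Background states that "Bisphosphonates are a class of drugs commonly used to treat osteoporosis". The trial enrols patients aged 50 to 75. Osteomalacia is an exclusion; osteoporosis is not.

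The outcomes that a bisphosphonate could move are the cartilage WORMS score at 6 and 12 months (primary) and at 24 months (secondary), and bone density measured "using dual-energy x-ray absorptiometry (DXA) at 12 and 24 months after enrollment".

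**The concern.** A trial of alendronate plus vitamin D3 against placebo needs a placebo group free of bisphosphonate effect. As written, someone who took a prescribed bisphosphonate until shortly before randomisation, and who agrees to stop, can enter either arm.

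If the earlier drug still acts after stopping, that patient shows less than the full difference between study drug and placebo. On placebo, some of the effect is already present; on alendronate, less is left to gain. Both pull the estimated difference toward zero. What is at stake is an understated estimate for the primary outcome and for bone density, not a false positive result.

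The omission is notable because the authors did write washouts for other drugs, in a complete numbered list, and left out the class being tested.

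**Working it through.** **Is there a look-back anywhere?** Setting the sections side by side:

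| Place in the protocol article | What it covers | Reaches earlier bisphosphonate use? |
|---|---|---|
| Study design and setting | Other bisphosphonates, on study | No, it starts with the study |
| Inclusion criteria (3) | Age and pain, diagnosis, imaging | No |
| Exclusion criterion 2, first part | NSAIDs and central analgesics, two weeks | No |
| Exclusion criterion 2, second part | Other study drug or device, 30 days or half-life | No; the plain sense is a product from another study, not a marketed prescription |
| Exclusion criterion 10 | Allergy or contraindication | No; earlier use is neither |
| Remaining exclusions | Disease, organ function, fracture, dental health and similar | None names the class |

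The word *other* in the on-study ban also leaves alendronate from outside the trial not expressly barred.

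**How large could the effect be?** The plan gives no figure on this point, so there is none to reproduce. Two inputs are needed, and the document supplies neither:

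- f, the share of recent users in each arm (assumed 5%, 10%, 15%; equal between arms on average because of randomisation);
- r, the fraction of the full contrast that a recent user loses (assumed 0, 0.5, 1).

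Let D be the contrast in patients without recent use, and assume that recent users would have had the same D but for carry-over. The average contrast is then

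D × [(1 − f) + f × (1 − r)] = D × (1 − f × r),

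so the relative attenuation is f × r:

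| | f = 5% | f = 10% | f = 15% |
|---|---|---|---|
| r = 0 | 0% | 0% | 0% |
| r = 0.5 | 0.05 × 0.5 = 2.5% | 0.10 × 0.5 = 5% | 0.15 × 0.5 = 7.5% |
| r = 1 | 5% | 10% | 15% |

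The r = 1 row is an upper bound for each f. The study tablet also contains vitamin D3, and earlier bisphosphonate use would not remove that part of the contrast.

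**Why no shift in points.** The Sample size calculation section's difference comes from vitamin D: a serum level that "has been reported to correlate with a 2.2% annual absolute reduction in cartilage loss". That is a cartilage-volume figure. The primary outcome is a cartilage score "with an overall score ranging from 0 to 84". The article gives no expected alendronate effect on that score and no SD, so D cannot be put in points and a power loss cannot be derived.

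**The case against.** The strongest reply is that the harm depends on two facts the document does not contain: that recent users will enrol, and that effects persist. With r = 0 the attenuation is nil. This stands, and it limits what can be claimed. Persistence is still not fanciful on the article's own terms. The Background cites a trial that gives zoledronate once a year, and this trial measures WORMS and bone density at 24 months, a year after its one-year course ends. Neither shows carry-over; both show that the sponsor cannot simply dismiss it.

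Second, the design probably keeps f low. Entry requires bone marrow edema-like lesions, which the article links to high bone turnover; a patient whose turnover is still suppressed by earlier treatment may be less likely to qualify. A treated patient would have to stop and accept an even chance of placebo. Recent fracture and serious endocrine disease are excluded. These are fair points, but none replaces a look-back.

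Third, a reader might infer from the bone-density analysis, which "will be analyzed as categorical outcomes (normal, low density, osteoporosis) using the Chi-square test", that patients with osteoporosis are expected. The document does not support that. These are outcome categories, in a sentence that also ties osteoporosis severity to the Kellgren-Lawrence scale, and osteoporosis would not in itself mean recent bisphosphonate use. Age and the absence of an osteoporosis exclusion make such patients possible, no more.

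Fourth, power may be little affected. Back-solving an SD from 30 per arm, a 2.2 difference, 80% power and two-sided 0.05 gives 2.2 / [(1.960 + 0.842) × √(2/30)] = 3.04. With 110 × 0.9 × 0.9 ≈ 89 per arm, even f = 30% and r = 1 (contrast 2.2 × 0.7 = 1.54) leaves about 92% power. This is only an illustration, since the SD is not stated and the 2.2 is on the wrong scale. It does suggest that the issue is the size of the estimate rather than a failed test.

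Fifth, the full protocol may hold washout rules. That carries little weight here, because the article prints a full numbered eligibility list with look-backs for other drugs.

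**Conclusion.** The gap is real: as written, recent users of a marketed bisphosphonate, including alendronate, are eligible for either arm. Confidence in that is high.

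Confidence in the size of any harm is low. If effects persist, the WORMS and bone-density contrasts are attenuated by f × r, which runs from 0% to 15% over the assumed ranges (f from 5% to 15%, r from 0 to 1).

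A reader might go further and conclude that the comparison is confounded or the trial invalid. That does not follow. Randomisation balances earlier use on average, the comparison stays valid, and type I error is not inflated. Nor does the document support a stated loss of power or of WORMS points. This is a cheap improvement to eligibility, not a flaw that undermines the trial.

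**What to change.** 1. Add an exclusion criterion for use of any bisphosphonate, oral or intravenous and including alendronate, within a fixed window before randomisation. Twelve months is an example only; it is an assumption, and the sponsor should justify the window on pharmacological grounds.
2. In Study design and setting, reword the on-study ban to cover any bisphosphonate other than study medication.
3. Enrolment was scheduled to start on May 1, 2021, and a new exclusion cannot remove patients already randomised. For them, record earlier bisphosphonate use (drug, route, last dose) and run a sensitivity analysis that adjusts for or excludes recent users. Excluding them, or adding a treatment-by-earlier-use term, addresses dilution directly; a covariate alone leaves the averaged contrast as it is.

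Cost: one protocol amendment, a medication-history check at screening, one extra data item and one sensitivity analysis. The downside is slightly fewer eligible patients.

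### Known osteoporosis is not an exclusion, so a patient with diagnosed osteoporosis can be assigned a placebo year in which the trial does not permit other bisphosphonates

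*Protocol article*

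**What the plan says.** All places are in the protocol article.

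- **Background** names the usual indication of the class: "Bisphosphonates are a class of drugs commonly used to treat osteoporosis".
- **Study design and setting** fixes the comparison: "Patients will undergo a 1:1 double-blinded randomization to receive a one-year course of" alendronate with vitamin D3, or placebo.
- **The same section** sets the rule on concomitant drugs: "Other bisphosphonates (such as zoledronic acid, risedronic acid, etc.) will be prohibited during the study period". No exception is given. It also states: "In addition, Vitamin D and calcium supplementation will be allowed for usage by study participants".
- **Inclusion criteria** admit patients aged 50 to 75 with knee pain, early radiographic osteoarthritis and bone marrow lesions on MRI. Bone density is not mentioned.
- **Exclusion criteria** are a numbered list of 13 items. The ones closest to bone disease or prior bone treatment are "4) having renal dysfunction, osteomalacia, or creatinine clearance < 35 mL/min", "8) having fracture within 6 months of study initiation" and, within item 2, "other study drug or device within 30 days before randomization or within the drug half-life (whichever is longer". Item 5 covers serious disease of several organ systems, endocrine disease among them.
- **Informed consent** and **Criteria for discontinuing allocated interventions** let patients leave whenever they wish, with no effect on their care.

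**The concern.** A placebo arm is hardest to defend for a patient who already has a recognised reason to take the active drug. Here the article itself names that reason, and the eligibility list does not remove patients who have it. The ban on other bisphosphonates closes the most direct way of treating such a patient inside the trial.

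At stake is the safety of a small subgroup, those whose osteoporosis is already diagnosed when they are screened. Patients whose osteoporosis nobody has yet found are a different matter, since nothing is knowingly withheld from them.

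**Working it through.** **Step 1. Does any exclusion cover known osteoporosis?** The candidates, one by one:

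| Item | What it removes | Does it cover known osteoporosis? |
|---|---|---|
| 2 | Recent users of NSAIDs, central analgesics, or another study drug or device | No. Neither osteoporosis nor bisphosphonate use is named |
| 4 | Renal dysfunction, osteomalacia, low creatinine clearance | No. Osteomalacia is a different bone disease |
| 5 | Serious endocrine and other systemic disease | Not reliably. Osteoporosis is not named, and sites could read the item differently |
| 8 | Fracture in the 6 months before the study | Only in part. Osteoporosis without a recent fracture passes |
| 10 | Allergy or contraindication to the study medication | No. Osteoporosis is an indication for the class |

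The other items concern inflammatory arthritis, liver function, pregnancy, upper gastrointestinal disease, tobacco and alcohol, imaging contraindications, planned joint replacement and dental health. None applies.

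**Step 2. What happens to such a patient once enrolled?** Allocation is 1:1, so the chance of placebo is 0.5. During the placebo year other bisphosphonates are not permitted. Vitamin D and calcium are, and no other class of osteoporosis drug is named as prohibited.

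**Step 3. How many patients?** Inputs: 220 enrolled, 110 per group (Sample size calculation; the Abstract still shows 60, but that section gives 220 as the final figure). The share *p* with known osteoporosis is not in the article and has to be assumed.

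Placebo patients affected = 220 × *p* × 0.5

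- *p* = 1%: 220 × 0.01 × 0.5 = 1.1
- *p* = 10%: 220 × 0.10 × 0.5 = 11

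The 1% to 10% range only illustrates scale. Nothing in the article supports one value over another.

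**Step 4. What would exclusion cost in recruitment?** Otherwise eligible patients needed to enrol 220 = 220 / (1 − *p*)

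- *p* = 1%: 220 / 0.99 = 222.2, so 223, which is 3 more
- *p* = 10%: 220 / 0.90 = 244.4, so 245, which is 25 more

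**The case against.** The strongest reply is that nobody is held in the trial against their interest. Patients can refuse or leave at any time with no effect on their care. The article attaches no stated consequence to starting a bisphosphonate, whereas it says that users of unmarketed or investigational drugs will be excluded. Other osteoporosis drug classes remain open, vitamin D and calcium are allowed, and the recent-fracture rule removes one visible high-risk group. The number affected is unknown and may be very small. All of this stands, and it limits the harm to a choice between staying in the trial and using this class. It does not close the gap: consent and withdrawal leave the patient to repair what an eligibility rule should settle at entry.

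It can also be said that an article condenses the full protocol. That carries little weight here, because the exclusions are given as a complete numbered list and the ban is stated outright.

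A reader might infer four stronger things, none of which the article supports:

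- *That placebo patients with osteoporosis go without any treatment.* Only bisphosphonates are named as prohibited among osteoporosis drugs.
- *That the primary result is biased.* Randomisation allocates these patients to both arms, and nothing in the article shows that the eligibility gap distorts the comparison of cartilage scores at 6 and 12 months.
- *That the sponsor plans to enrol known cases, because Statistical analysis lists osteoporosis as a bone density category.* That category could hold cases first found on the DXA scans at 12 or 24 months.
- *That patients are barred from the class for the full two years of follow-up, or left untreated if the month-12 scan shows osteoporosis.* The article does not define the study period or describe such cases, and those details commonly sit in the full protocol. The point here needs only the placebo year.

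**Conclusion.** The point holds in a limited form. Under the eligibility rules as written, a site can knowingly randomise a patient with diagnosed osteoporosis to a year of placebo during which the trial does not permit the drug class that the article itself links to that disease. The consequence is loss of access to one class while the patient stays in the trial.

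The size is unknown. It is about 1 placebo patient for each 1% of the 220 enrolled who have known osteoporosis, given 1:1 allocation and enrolment of the full 220. The case for a change does not depend on the share, since it applies to a single patient. No effect on the validity of the primary analysis is asserted. This is a cheap improvement.

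**What to change.** Add one item to the Exclusion criteria: *known (diagnosed) osteoporosis, from medical history or an already available DXA report*. Tying it to an existing diagnosis gives the three hospitals a rule that they can apply in the same way, and no screening scan is added.

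The cost is slightly slower recruitment (3 to 25 more otherwise eligible patients under the assumed 1% to 10%) and a slightly narrower population, since the results would no longer speak directly to patients with knee osteoarthritis and diagnosed osteoporosis. Outcomes, visits and analyses stay as they are.
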